## Information Collected and Observation Items

### Observation Item and Method

1. **Obtaining Written Consent and Assigning Enrollment Numbers to Study Subjects**

Before collecting data related to this study, the investigator must explain the purpose and details of the study to the study subjects through an information sheet and obtain voluntary consent. This consent must include the subject's name, signature, and the signing.

The date of written consent and Visit 1 (Baseline, Day 0) may differ, but consent must be obtained before participation in the clinical study.

Enrollment numbers for subjects are automatically assigned in the eCRF upon obtaining consent. Subject numbers are 6 digits and formatted as “AXX-ZZZ”, where:

- “A”: Classification code
- “XX”: Institution number (001, 002 -)
- “ZZZ”: Subject number at each institution in the order of consent (001, 002 -)

1. **Inclusion/Exclusion Criteria Confirmation**

Inclusion/Exclusion criteria are confirmed at Visit 1 (Baseline, Day 0) to verify if all inclusion criteria are met and none of the exclusion criteria apply.

1. **Demographic Information**

At Visit 1 (Baseline, Day 0), the following information is collected to verify the subject's basic information. Pregnancy status is collected through interview or existing pregnancy test results, if available.

- Initials
- Gender
- Birth month and year, Age (in full years)
- Pregnancy and breastfeeding status

1. **Information on Type 2 Diabetes**

At Visit 1 (Baseline, Day 0), the diagnosis date of Type 2 diabetes will be collected to confirm the purpose of administering Envlo Tab. or Envlomet SR Tab.

1. **Medical History Review**

For medical history, any clinically significant medical conditions or abnormalities observed before Visit 1 (Baseline, Day 0), excluding the target disease, will be defined. The diagnosis name and date of each condition will be collected for medical history within 6 months prior to Visit 1 (Baseline, Day 0) and ongoing conditions.

1. **Alcohol/Smoking/Lifestyle Information**

At Visit 1 (Baseline, Day 0), the following information is collected to verify the subject's basic information, and any changes will be additionally collected at each subsequent visit.

1. Drinking history
   - Current Drinker^*^: ≥ 12 glasses (units) in a lifetime and drinking at least once in the last 12 months
   - Former Drinker: Has consumed at least 12 units of alcohol in their lifetime but has not drunk in the past 12 months
   - Non-Drinker: < 12 glasses (units) in a lifetime

^*^ For current drinkers, the weekly drinking frequency and amount per occasion will be confirmed.

1. Smoking history
   - Current Smoker: Has smoked at least 5 packs (100 cigarettes) in their lifetime and smoked within the past 30 days
   - Former Smoker: Has smoked at least 5 packs (100 cigarettes) in their lifetime but has not smoked within the past 30 days
   - Non-smoker: Has smoked < 5 packs (100 cigarettes) in a lifetime
2. Lifestyle (Dietary Habits): Irregular meals, overeating, excessive intake of carbohydrate/sugar, excessive fat intake, excessive salt intake
3. Lifestyle (Exercise Habits): Types of exercise (walking, aerobic exercise, strength training), weekly exercise frequency, exercise intensity (less than 30 minutes, up to 1 hour, long duration)
4. **Physical Measurement**

Weight will be collected at every visit, while height will be collected once at Visit 1 (Baseline, Day 0).

1. **Vital Signs**

At every visit, the following vital signs will be collected:

- Blood pressure (systolic/diastolic)
- Pulse Rate

Blood pressure and pulse should be measured in a quiet environment after at least 5 minutes of rest in a chair with a backrest. The subject should refrain from smoking, alcohol, and caffeine intake for at least 30 minutes prior to measurement, if possible. Any clinically significant abnormalities and results that meet the definition of an adverse reaction will be collected as adverse events.

1. **Body Composition Analysis**

Body composition analysis will be performed using the InBody770 device. Measurements will be taken at Visit 1 (Baseline, Day 0), Visit 2 (Follow-Up Visit, 12 weeks), and Visit 3 (Close-out Visit, 24 weeks) at institutions capable of conducting these measurements. The following parameters will be included to the extent possible:

- Body Mass Index
- Skeletal muscle mass
- Body fat mass
- Body fat percentage
- Waist/hip circumference
- Other indices (body water, intracellular water, extracellular water, extracellular water ratio, abdominal fat percentage, etc.)

1. **Prior/Concomitant Medications**

For concomitant medications, collect information only for diabetes medications administered within 4 weeks prior to Visit 1 (Baseline, Day 0). Collect information on medications taken consistently for over 3 months at Visit 1 (Baseline, Day 0).

- Drug Name (Brand Name)
- Dosage and Administration (Dose per administration, unit, frequency, route)
- Duration of Administration (Start date, end date, ongoing status)
- Purpose of Administration
- Reason for Dose Adjustment or Discontinuation (if applicable)

1. **Laboratory Tests**

Laboratory tests are collected based on standard clinical procedures in a real-world clinical setting. If there are HbA1c results within 4 weeks prior to Visit 1 (Baseline, Day 0) or other test results collected within 3 months, these results can be used as substitutes for the laboratory tests at Visit 1 (Baseline, Day 0).

HOMA-beta is calculated using the formula [360×fasting insulin concentration (μU/mL)×fasting glucose (mg/dL)-63], and HOMA-IR is calculated with [fasting insulin concentration (μU/mL)×fasting glucose (mg/dL)/405].

Examples of Laboratory Test Items to be Collected:

| Main Laboratory Tests | HbA1c, FPG, Creatinine, eGFR, TC (Total Cholesterol), HDL, LDL, TG (Triglyceride), UACR, UGCR |
| --- | --- |
| Other Laboratory Tests  (Blood Tests) | RBC, Hemoglobin, Hematocrit, Platelet, WBC, Differential WBC count (Basophil, Eosinophil, Neutrophil, Lymphocyte, Monocyte), Na, K, Cl, P, Ca, Mg, BUN, LDH, Uric Acid, ALT, AST, ALP, γ-GTP, CPK, Total Bilirubin, Albumin, Total Protein, Glucose^*^, Insulin^*^ |
| Other Laboratory Tests  (Urinalysis) | pH, Specific Gravity, Bilirubin, Ketone, Nitrite, Protein (Albumin), RBC (Occult Blood), Urobilinogen, WBC (Leukocyte), Glucose, Creatinine |

1. **Investigational Product Administration Information**

To verify the administration details of the investigational product in this study, collect the following items at each visit:

- Medication Name (Envlo Tab. or Envlomet SR Tab.)
- Dosage and Administration (Dose per administration, unit, frequency)
- Duration of Administration (Start date, end date, ongoing status)
- Presence of Dose Adjustment or Discontinuation
- Reason for Dose Adjustment or Discontinuation (if applicable)

1. **Adverse Event**

Collect all adverse events from the start of investigational product administration until the end of the study to evaluate the safety of the investigational product and ensure the safety of the subjects.

- Occurrence of Adverse Events
- Adverse Event Information
- Name of Adverse Event
- Date of onset and resolution of Adverse Event
- Presence of Serious Adverse Event
- Presence of Unexpected Adverse Event
- Severity
- Course of Adverse Event
- Causal Relationship with the Investigational Product
- Actions Taken Related to the Investigational Product
- Actions Taken Other than the Investigational Product
- Investigator

Adverse events occurring or ongoing at the end of Visit 3 (close-out visit at 24 weeks) will be followed up until resolution or until the investigator determines that further follow-up is no longer meaningful. For subjects who withdraw from the study before the 24-week period, adverse events will be collected up to 30 days after the withdrawal.

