4. Collect physical measurements (height) and body composition analysis information. Height is collected only at Visit 1 (Baseline, Day 0) to the first decimal place. Body composition analysis (skeletal muscle mass, body fat mass, body fat percentage, waist/hip circumference, etc.) is collected at each visit using InBody770.
5. After at least 5 minutes of rest, collect vital signs (systolic blood pressure, diastolic blood pressure, pulse rate). If there are measurement results at each visit, collect these results.
6. Collect information on Type 2 diabetes (date of diagnosis).
7. For medical history, collect past medical history within 6 months prior to Visit 1 (Baseline, Day 0) and current medical conditions at the time of enrollment.
8. Laboratory tests are collected if conducted as part of routine clinical practice. If there are HbA1c results within 4 weeks prior to Visit 1 (Baseline, Day 0) or other test results within 3 months prior to Visit 1, these results can be used in place of the laboratory tests at Visit 1 (Baseline, Day 0). Examples of laboratory test items are as follows.

| Main Laboratory Tests | HbA1c, FPG, Creatinine, eGFR, TC (Total Cholesterol), HDL, LDL, TG (Triglyceride), UACR, UGCR |
| --- | --- |
| Other Laboratory Tests  (Blood Tests) | RBC, Hemoglobin, Hematocrit, Platelet, WBC, Differential WBC count (Basophil, Eosinophil, Neutrophil, Lymphocyte, Monocyte), Na, K, Cl, P, Ca, Mg, BUN, LDH, Uric Acid, ALT, AST, ALP, γ-GTP, CPK, Total Bilirubin, Albumin, Total Protein, Glucose^*^, Insulin^*^ |
| Other Laboratory Tests  (Urinalysis) | pH, Specific Gravity, Bilirubin, Ketone, Nitrite, Protein (Albumin), RBC (Occult Blood), Urobilinogen, WBC (Leukocyte), Glucose, Creatinine |

*According to the calculation formulas, HOMA-beta is calculated as [360×fasting insulin concentration (μU/mL)×fasting glucose (mg/dL)-63], and HOMA-IR is calculated as [fasting insulin concentration (μU/mL)×fasting glucose (mg/dL)/405].

1. - Prior medications: Collect information on diabetes medications used specifically for the treatment of Type 2 Diabetes within 4 weeks prior to Visit 1 (Baseline, Day 0). This includes the drug name (generic or brand name), duration of administration (start date, end date, ongoing status), single dose amount/unit, daily administration frequency, and route of administration.

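### As printed, HOMA-beta is HOMA-IR rescaled (145,800 × HOMA-IR − 63); the formula needs correcting in two places, with limited consequence

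*Protocol*

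**What the plan says.** The protocol gives the two HOMA formulas twice, in the same form each time.

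- Section 4.4, Observation Item and Method, Laboratory Tests: "HOMA-beta is calculated using the formula [360×fasting insulin concentration (μU/mL)×fasting glucose (mg/dL)-63", and in the same sentence "HOMA-IR is calculated with [fasting insulin concentration (μU/mL)×fasting glucose (mg/dL)/405". Where the two formulas meet, the text reads "fasting glucose (mg/dL)-63], and HOMA-IR is calculated with", so the 63 is the last term inside the HOMA-beta bracket.
- Schedule for Data Collection in Observational Study, the footnote to the asterisked glucose and insulin items in the laboratory table: "HOMA-beta is calculated as [360×fasting insulin concentration (μU/mL)×fasting glucose (mg/dL)-63", followed by "HOMA-IR is calculated as [fasting insulin concentration (μU/mL)×fasting glucose (mg/dL)/405".

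In both places a multiplication sign stands between insulin and glucose in HOMA-beta, and no inner bracket ties the 63 to glucose. The protocol gives no other HOMA-beta formula and attaches no reference to either index.

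On how the inputs arise, section 4.4 says: "Laboratory tests are collected based on standard clinical procedures in a real-world clinical setting". Insulin appears only in the table of example laboratory items, among the other blood tests.

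**The concern.** HOMA-beta is meant to describe beta-cell function and HOMA-IR insulin resistance. A protocol that derives both expects two pieces of information. The printed formulas use the same product, insulin × glucose, and differ only by a multiplier and a constant, so the second index adds nothing to the first.

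The printed HOMA-beta also rises when glucose rises at a given insulin. A programmer who followed the text would produce values on an implausible scale, and their change over 24 weeks would be the HOMA-IR change under another name. These are derivation rules in the data collection sections, not background text, so they are likely to be followed as they stand.

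**Working it through.** **Inputs.** The two formulas come from section 4.4 and from the schedule footnote. The protocol reports no insulin or glucose values, so every value below is an assumption chosen to show the scale. It also states no HOMA result to reproduce.

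**Step 1: algebra on the printed formulas.** Let P = fasting insulin × fasting glucose.

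- HOMA-IR = P / 405, so P = 405 × HOMA-IR.
- Printed HOMA-beta = 360 × P − 63 = 360 × 405 × HOMA-IR − 63 = 145,800 × HOMA-IR − 63.

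This holds for every subject and visit, so the correlation is exactly 1.

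**Step 2: consequence for a test on change.** In a within-subject change the constant 63 cancels, so change in HOMA-beta = 145,800 × change in HOMA-IR. The paired t statistic does not depend on a positive scale factor, and neither do the signs and ranks in the Wilcoxon signed rank test. Each test gives the same p-value for both indices.

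**Step 3: size.** The last column is the quotient form, 360 × insulin / (glucose − 63).

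| Insulin (µU/mL) | Glucose (mg/dL) | HOMA-IR | Printed HOMA-beta | Quotient form |
|---|---|---|---|---|
| 2 | 100 | 0.49 | 71,937 | 19.5 |
| 5 | 126 | 1.56 | 226,737 | 28.6 |
| 10 | 150 | 3.70 | 539,937 | 41.4 |
| 15 | 150 | 5.56 | 809,937 | 62.1 |
| 30 | 250 | 18.52 | 2,699,937 | 57.8 |

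For insulin 2 to 30 and glucose 100 to 250 the printed formula runs from 71,937 to 2,699,937, and the quotient form from about 4 to 292.

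**Step 4: is it only a missing bracket?** At insulin 10 and glucose 150 the subtracted 63 is 63 / 540,000, about 0.01% of the product, so it does nothing where it stands. Adding the inner bracket alone gives 360 × 10 × (150 − 63) = 313,200. Both the bracket and the division are needed: 360 × 10 / (150 − 63) = 41.4.

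**Step 5: direction of change.** Let glucose fall from 150 to 120.

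- Insulin constant at 10: the printed value goes from 539,937 to 360 × 10 × 120 − 63 = 431,937 (−20%). The quotient form goes from 41.4 to 360 × 10 / 57 = 63.2 (+53%).
- Insulin free to change: the printed value falls while the insulin ratio (follow-up / baseline) is below 150 / 120 = 1.25. The quotient form rises while that ratio is above 57 / 87 = 0.655.
- The two forms therefore move in opposite directions for insulin changes between about −34% and +25%. Below that range both fall; above it both rise.

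Other assumed glucose falls give similar ranges. From 200 to 150 the limits are 87 / 137 = 0.635 and 200 / 150 = 1.33. From 126 to 100 they are 37 / 63 = 0.587 and 126 / 100 = 1.26.

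**The case against.** The strongest case on the other side concerns weight, and most of it stands. Neither HOMA index appears among the primary, secondary, exploratory or safety endpoints, in the synopsis, in sections 2.1 to 2.4 or in section 8.1. Insulin is not named in the visit lists of section 4.3, and no test is mandatory, so the indices may be computable for few subjects at primary care sites. The only analysis text that could reach them is the general laboratory paragraph of section 8.2, which does not name them. Values near 540,000 would also be likely to draw a query under the data checks of section 7.2. That lowers the risk but leaves the text wrong.

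A reader might infer that the direction of the treatment effect would be reversed. The documents do not support this. No treatment effect on HOMA-beta is planned, the glucose and insulin values are assumed, and Step 5 shows that the reversal depends on how insulin changes. Section 1.1 itself says that the drug class brings a relative decrease in insulin secretion, so constant insulin cannot be taken for granted. Nor are all printed values in the hundreds of thousands, as the table shows.

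It can also be said that the quotient form appears nowhere in the protocol. That is so, and the replacement has to be checked against the published definition. The duplication of HOMA-IR needs no outside source.

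Loss of a sign in text conversion is an unlikely explanation. A multiplication sign is printed in that position in both places, the inner bracket is missing in both, and the slash in HOMA-IR survived in the same sentence.

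**Conclusion.** The formula is wrong as written in both places. On the protocol's own definitions, HOMA-beta = 145,800 × HOMA-IR − 63, so it carries no information beyond HOMA-IR. This is exact and rests on no assumption. The scale comparison (539,937 against 41.4) rests on the assumed insulin and glucose and on the quotient form as the intended index. The opposite movement for a glucose fall from 150 to 120 holds only for insulin changes between about −34% and +25%.

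The point is minor. No listed endpoint depends on the formula, and the primary analysis of weight and BMI and the sample size are unaffected. The SAP was not available; a correct formula there would still leave two wrong ones in the protocol.

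**What to change.** In section 4.4 (Laboratory Tests) and in the laboratory footnote to the data collection schedule, correct HOMA-beta against its standard published definition by restoring the division and the inner bracket:

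HOMA-beta = [360 × fasting insulin (µU/mL)] / [fasting glucose (mg/dL) − 63]

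Cite the source next to it. Leave HOMA-IR unchanged. Make the same correction in any program that derives the index; the protocol does not say where the derivation takes place, so this has to be checked.

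The cost is one line in two places, plus approval of the amendment by the review board. No visit, test, endpoint or sample size changes.

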# Information on Investigational Product

The administration of the investigational product in this observational study is determined by the investigator (responsible physician) based on the actual clinical setting and the situation of each subject.

Therefore, only basic information within the scope of the product description and approval is detailed in the study protocol.

The investigator will appropriately decide on the treatment dose considering the investigational product's approved indications and the subject's medical condition, referring to the product description for detailed information.

|  | **Envlo Tab. 0.3 mg** | **Envlomet SR Tab. 0.3/1,000 mg** |
| --- | --- | --- |
| Manufacturer | Daewoong Pharmaceutical Co., Ltd. | Daewoong Pharmaceutical Co., Ltd. |
| Active Ingredient and Content | Enavogliflozin 0.3 mg | Enavogliflozin 0.3mg, Metformin 1,000 mg |
| Appearance | Pale-orange, biconvex, triangular, film-coated tablet | White and light pink, oval-shaped, bilayer sustained-release tablet |
| Efficacy and Effect | Administered as an adjunct to diet and exercise regimens to improve glycemic control in patients with Type 2 Diabetes  - Monotherapy  - Combination therapy | As an adjunct to diet and exercise to improve glycemic control in patients with Type 2 Diabetes mellitus for whom the combination of Enavogliflozin and metformin is appropriate |
| Regimen and Dose | 1 tablet once daily | 1 tablet once daily |
| Storage Condition | Store in a tight container at room temperature (1–30℃) | Store in a tight container at room temperature (1–30℃) |

## Expected Adverse Events (Side Effects) and Precautions for Use

1. Do not administer to the following patients:

- Current or history of hypersensitivity to the active ingredient or components of this drug
- Patients with Type 1 Diabetes (T1D) or diabetic ketoacidosis
- Patients with an eGFR < 30 mL/min/1.73 m2, end-stage renal disease, or on dialysis
- Patients with moderate and severe liver dysfunction

# Adverse Event

## Definition of Adverse Event

1. **Definition of Terms**
2. **Adverse Event**

An AE refers to any unfavorable and unintended sign (including an abnormal laboratory test finding), symptom, or disease that has occurred in a subject after obtaining informed consent, which does not necessarily have to have a causal relationship to the investigational product.

1. **Adverse Drug Reaction (ADR)**

Refers to any untoward and unintended response to the investigational product of any dose, of which causal relationship to the investigational product cannot be excluded.

1. **Serious Adverse Event/Serious Adverse Drug Reaction(SAE/SADR)**

Refers to an AE or an ADR at any dose of the investigational product that:

1. Death
2. Hospitalization or prolongation of existing hospitalization
3. Congenital anomaly or birth defect
4. Life-threatening
5. Significant disability/incapacity
6. Any other medically significant condition

However, the following hospitalizations are not considered SAEs:

- Planned hospitalization for treatment for a pre-existing condition that has not worsened from baseline
- Hospitalization scheduled before the study subject signed informed consent or for planned tests, etc.
- Elective hospitalization (e.g., admission for cosmetic surgery)
- Emergency room visits (However, it shall be considered as hospitalization: hospitalization is confirmed after visiting the emergency room and the patient is moved to a floor; or hospitalization is confirmed after visiting the emergency room, but the patient stays in the emergency room due to a lack of available hospital beds.)

1. Unexpected Adverse Event (Unexpected AE)

Refers to an AE that is not reflected in the precautions for use.

1. **Unexpected Adverse Drug Reaction**

Refers to an ADR that differs in its nature, severity, specificity, or outcome compared to the marketing approval of the drug.

## Evaluation of Adverse Event

1. **Severity of Adverse Events**

The severity of AEs should be evaluated according to the following criteria:

1. Mild: Subjective or objective symptoms are present but do not interfere with daily activities
2. Moderate: Symptoms interfere with daily activities to the extent that treatment is required
3. Severe: Symptoms prevent normal daily activities. Strong adverse events necessitate medical intervention and may require hospitalization.
4. **Outcome of Adverse Event**
5. Recovered/Resolved
6. Recovering/Resolving
7. Not recovered/Not resolved
8. Recovered/Resolved with sequelae
9. Death due to ADR/AE (Fatal)
10. Unknown
11. **Causal Relationship**

The causal relationship between administration of the IP and onset of the AE will be determined by the investigator based on their clinical judgment. Since the causality to the IP cannot be tested statistically, it will be assessed based on personal situation, medical (physiological, pathological, and pharmacological) possibility, literature, etc. and it will also be helpful to consider temporal relationship. In addition, disappearance or reappearance upon discontinuation or re-administration of the investigational product, concomitant medications, etc. will be considered.

At this time, the following criteria can be used as indicators for assessment: Certain, Probable, Possible, Conditional/Unclassified, and Unassessable/Unclassifiable. If evaluated as Certain, Probable, Possible, Conditional/Unclassified, or Unassessable/Unclassifiable, the event is considered to be related. If evaluated as Unlikely or Not Related, the event is considered to be not related.

1. Certain: A plausible temporal relationship with the investigational product, not explained by other drugs, chemicals, or underlying conditions. A clinically reasonable response to withdrawal of the investigational product, and a pharmacologically or phenomenologically definitive response to re-administration, if necessary.
2. Probable: A reasonable temporal relationship with the investigational product, unlikely to be explained by other drugs, chemicals, or underlying conditions. A clinically reasonable response to withdrawal of the investigational product (without re-administration information)
3. Possible: A reasonable temporal relationship with the investigational product, but could also be explained by other drugs, chemicals, or underlying conditions. Information about withdrawal of the investigational product is lacking or unclear
4. Unlikely: A temporary case with improbable causal relationship with the administration/use of the investigational product, and can be reasonably explained by other drugs, chemicals, or underlying conditions
5. Not Related: No administration of the investigational product, or the temporal relationship of adverse event is not plausible, or the adverse event can be more likely explained by other factors
6. Conditional/Unclassified: More data is needed for appropriate evaluation, or additional data is under review.
7. Unassessable/Unclassifiable: Information is insufficient or conflicting, making a judgment impossible, and cannot be supplemented or verified
8. **Actions Taken with the Investigational Product**
9. Drug withdrawn
10. Dose reduced
11. Dose increased
12. Dose not changed
13. Unknown
14. Not applicable
15. **Actions taken for Adverse Events**
16. Concomitant medication therapy
17. Non-medication therapy
18. Concomitant medication therapy/non-medication therapy
19. No concomitant medication therapy/non-medication therapy

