# Evaluation Criteria and Methods, and Statistical Analysis Methods

## Endpoints

1. **Efficacy Endpoints**
2. **Primary Efficacy Endpoint**

- Change in BMI and weight at 24 weeks compared to baseline

1. **Secondary Efficacy Endpoints**
2. Change in BMI and weight at 12 weeks compared to baseline
3. Proportion of subjects achieving ≥ 5% reduction in BMI and weight at 12 and 24 weeks compared to baseline
4. Change in body composition analyzer indicators (body fat mass, visceral fat mass, muscle mass, waist/hip circumference, etc.) at 12 and 24 weeks compared to baseline
5. Change in HbA1c at 12 and 24 weeks compared to baseline
6. Change in FPG at 12 and 24 weeks compared to baseline
7. Proportion of subjects achieving HbA1c < 7% at 12 and 24 weeks compared to baseline
8. Proportion of subjects achieving HbA1c < 6.5% at 12 and 24 weeks compared to baseline
9. Proportion of subjects achieving therapeutic response [change in HbA1c (baseline HbA1c – HbA1c at each evaluation time point) > 0.5% or HbA1c < 7%] at 12 and 24 weeks compared to baseline
10. **Exploratory Endpoints**
11. Change in lipid levels (total cholesterol, LDL-C, HDL-C, triglycerides) at 12 and 24 weeks compared to baseline
12. Change in liver function markers (AST, ALT, γ-GTP) at 12 and 24 weeks compared to baseline
13. Change in renal function markers (e-CFR, UACR (Urine Albumin to Creatinine Ratio), UGCR (Urine Glucose to Creatinine Ratio)) at 12 and 24 weeks compared to baseline
14. Change in other body composition analyzer indicators (body water, intracellular water, extracellular water, extracellular water ratio, abdominal fat percentage, etc.) at 12 and 24 weeks compared to baseline
15. **Safety Endpoints**
16. Definition of an adverse drug reaction (ADR)
17. Incidence rate and number of occurrences of Serious ADRs (SADRs)
18. Adverse events of Special Interest^*^

* Hypoglycemia, urinary tract infection, genital infection, frequent urination, polyuria

1. Laboratory tests, vital signs, physical examination results

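### The causality categories overlap at the line between counted and not counted, and their mapping is narrower than the protocol's own definition of an adverse drug reaction

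*Protocol*

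**What the plan says.** Section 6.1 (Definition of Adverse Event) defines an ADR as an untoward, unintended response to the product "of which causal relationship to the investigational product cannot be excluded".

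Section 6.2 (Evaluation of Adverse Event, Causal Relationship) leaves causality to the investigator's clinical judgment and offers a scale as an aid. Three entries on the scale matter here:

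- "Possible: A reasonable temporal relationship with the investigational product, but could also be explained by other drugs, chemicals, or underlying conditions".
- "Unlikely: A temporary case with improbable causal relationship with the administration/use of the investigational product", with the further condition that another cause reasonably explains the event.
- Not Related, which has three alternatives joined by *or*: the product was not given; the timing is not plausible; "or the adverse event can be more likely explained by other factors".

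The same section turns the scale into a yes/no count: "If evaluated as Certain, Probable, Possible, Conditional/Unclassified, or Unassessable/Unclassifiable, the event is considered to be related". On the other side, "If evaluated as Unlikely or Not Related, the event is considered to be not related".

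The synopsis and Section 2.4 (Safety Assessment) name the incidence and number of ADRs, and of serious ADRs, as the first two safety endpoints. Section 8.2 (Adverse Event) tabulates both with 95% confidence intervals. In Section 8.1 (Endpoints) the ADR item instead begins "Definition of an adverse drug reaction (ADR".

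**The concern.** A causality scale that feeds a count has to place each event on one side of the line. Here the last alternative of Not Related reaches into the ground covered by Possible, and the two ratings are counted in opposite ways. The rating that should be hardest to give is also easier to reach than the milder Unlikely.

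Separately, the count built from Section 6.2 does not follow the definition in Section 6.1. The ADR and serious ADR rates would then be reported under a definition that the plan did not apply.

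This has to be settled in the protocol. Causality is judged at 12 primary care sites and entered in the eCRF. Once events are rated, no later analysis can tell which Not Related entries rested on the third alternative.

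**Working it through.** No arithmetic settles this point, so the check sets the definitions side by side.

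| Category (Section 6.2) | Condition on exposure, timing or link | Condition on other causes | Counted as |
|---|---|---|---|
| Possible | Timing reasonable | Another cause could also explain it | Related |
| Unlikely | Causal link improbable | Another cause reasonably explains it | Not related |
| Not Related, alternative 1 | Product not given | None | Not related |
| Not Related, alternative 2 | Timing not plausible | None | Not related |
| Not Related, alternative 3 | None | Another cause is the more likely one | Not related |

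**Step 1, overlap.** Take a treated patient with an event whose timing fits and for which another cause is more likely than the drug. If another cause is more likely, it certainly could explain the event, so the wording of Possible is met. Alternative 3 of Not Related is met as well. The event is counted under the first rating and dropped under the second, and the text gives no rule for choosing.

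**Step 2, order of the tests.** Unlikely needs an improbable causal link as well as another reasonable explanation. Alternative 3 needs only that the other explanation be the more likely of the two. A rival cause can be more likely while the drug remains a realistic candidate. The stronger label therefore has the weaker requirement.

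**Step 3, against Section 6.1.** That section asks whether causality can be excluded. An improbable link is not an excluded one, and neither is a link that is merely less likely than a rival. Alternatives 1 and 2 come close to exclusion; alternative 3 and Unlikely do not. Measured against Section 6.1, counting these two as not related can only take events out of the ADR total.

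**Step 4, lead-in.** The sentence that introduces the scale names five categories: Certain, Probable, Possible, Conditional/Unclassified and Unassessable/Unclassifiable. The definitions that follow number seven. The two left out of the lead-in are Unlikely and Not Related, the two that remove events from the count.

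**Step 5, size.** Let *x* be the subjects with an ADR under Section 6.1 and *y* those among them whose only such events are rated Unlikely or Not Related by alternative 3. With *N* subjects in the safety set, the reported incidence is (*x* − *y*)/*N* instead of *x*/*N*. The protocol gives neither *x* nor *y*, so no figure follows.

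**The case against.** **The scale is only an aid.** Section 6.2 offers the criteria as indicators under clinical judgment, and an investigator may well choose Possible. Conditional and Unassessable events also count as related, which pushes the count up. This stands. A reader might infer that ADR incidence is understated as a matter of fact; the protocol supports only that it can be.

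**The wording may be meant as a gradient.** Another cause that *could* explain the event would give Possible; a *more likely* one would give Not Related. That is a fair reading, and it means that a rival explanation alone does not trigger the third alternative. But the text does not limit Possible to rivals that are less likely than the drug, and the gradient would pass straight over Unlikely.

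**Expected reactions are not lost.** A reader might infer that hypoglycemia, urinary or genital infection, frequent urination and polyuria drop out of the safety results, because diabetes or other glucose-lowering drugs offer a rival cause. The documents do not support this. These are a separate endpoint, labelled adverse events and not limited to related ones. Section 8.2 also tabulates all adverse events and summarizes causality. Such events could leave only the ADR and serious ADR counts.

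**One event does not meet three categories.** That too might be inferred. Unlikely needs an improbable link, which fitting timing plus a rival cause does not establish. Overlap between Unlikely and Not Related would not change the count in any case.

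**The Section 8.1 line is a slip.** The synopsis, Section 2.4 and Section 8.2 make clear that ADR incidence is meant. Agreed: this is editorial and does not bear on the categories.

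**Conclusion.** The point holds as a contradiction in definitions. Possible and the third alternative of Not Related can both describe one event, with opposite effects on the ADR count. The treatment of Unlikely and of that alternative is narrower than the Section 6.1 definition. ADR and serious ADR counts can therefore be understated against the protocol's own definition, and they may differ between investigators for reasons of reading rather than risk.

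The size is unknown. It depends on the ADR rate and on the share of events with fitting timing and a more likely rival cause, and the protocol gives neither. The consequence is confined to the ADR and serious ADR counts. The conclusion rests on reading the definitions as written; investigators who apply the scale more cautiously would reduce the effect.

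**What to change.** 1. In Section 6.2, make the categories mutually exclusive. Either delete the third alternative of Not Related, leaving no exposure or implausible timing, or reword it to require that a causal link be excluded.
2. Make Sections 6.1 and 6.2 agree on whether Unlikely counts as an ADR. Step 1 is not enough by itself, because events could move from Not Related to Unlikely, which is also not counted.
3. In Section 8.2, present ADR and serious ADR incidence with and without Unlikely. Causality is already recorded, so this needs no new data, provided that the eCRF keeps the category and not only the related/not related result.
4. Name all seven categories in the lead-in to the scale.
5. Editorially, align the ADR item in Section 8.1 with the synopsis and Section 2.4.

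The cost is wording in Sections 6.1, 6.2, 8.1 and 8.2 and one extra table column, with no added visits or tests. The reported ADR rate may be somewhat higher. Counting Unlikely would also bring in events judged improbable, which is why both versions should be shown. Differences in clinical judgment between sites will remain, but they would no longer be built into the definitions.
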